### Study Design

This study uses a randomized experimental design with a between-subjects factor and a within-subject repeated-measures component over an 8-week follow-up period. Participants will be randomly assigned to 1 of 2 exposure conditions: a real natural environment or an immersive VR-simulated natural environment. Cognitive performance, emotional well-being, nature connectedness, and ADHD symptomatology will be assessed both before and immediately after exposure, with additional follow-up assessments conducted over the next 8 weeks, while brain activity will be continuously recorded during the exposure session.

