Resting-state baselines will be collected preexposure and postexposure (T0 and T1) with 2-minute eyes-open (fixation cross) and 2-minute eyes-closed recordings while participants sit quietly, instructed to stay relaxed, minimize blinking, and avoid large movements. During the 20-minute nature or VR exposure, EEG will be recorded continuously while participants remain seated; they will be reminded that they may pause or terminate the session if they experience discomfort, and any early termination will be documented and treated as dropout for EEG analysis. Evidence from previous VR-EEG studies [83] and from our own pilot testing indicates that simultaneous use of the FLEX cap and the VR headset is safe and allows reliable signal acquisition. Nevertheless, because VR head-mounted display padding can occasionally impinge on frontal or frontopolar sites, headset fitting will follow a predefined substitution protocol: if AF3/AF4 are partially obstructed, frontal alpha asymmetry will be computed from the canonical F3/F4 pair; if Fp1/Fp2 cannot be used, priority will be given to maintaining midline integrity at Fz. For any substituted electrodes, 3D electrode positions will be digitized to allow offline correction of spatial shifts, and the midline chain Fz-Cz-Pz-Oz will be preserved in all participants for core spectral and ERP analyses.

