Raw data will be exported from the proprietary EMOTIV format and converted to European Data Format/BioSemi Data Format for analysis. Offline preprocessing will be performed in EEGLAB and FieldTrip, using a 0.1 to 45 Hz finite-impulse-response band-pass filter and a 50 Hz notch filter to remove mains interference while preserving upper-beta activity relevant for theta/beta ratio outcomes. Data will then be re-referenced to the average of all scalp channels. Continuous recordings will be visually inspected to mark gross artifacts (eg, cable pops or sudden movement) and sections with poor contact. Independent component analysis will be applied to identify and remove stereotyped ocular and muscle components, following established guidelines for mobile and VR EEG. Remaining data will be segmented into 2-second nonoverlapping epochs for resting-state spectral analyses and into −200 to 800 ms epochs time locked to task stimuli or responses for ERP measures (N2/error-related negativity, P3, and related indices). Epochs showing extreme amplitudes or improbable distributions (as indexed by EEGLAB joint-probability and kurtosis metrics) will be rejected, ensuring that only artefact-free data contribute to power and ERP estimates.

To address concerns about VR-specific noise, exposure sessions will be conducted with participants seated, with head and body motion restricted to comfortable postural adjustments. Headset straps will be adjusted to avoid direct pressure on electrodes, and any pressure-related noise will be monitored online via impedance checks and offline via topographical inspection. Because the same EEG hardware, montage, and preprocessing pipeline are used in both exposure conditions, any residual artifacts linked to the outdoor environment (eg, occasional muscle adjustments due to temperature) or to the VR headset will be treated symmetrically and accounted for at the analysis stage (eg, sensitivity analyses excluding highly contaminated channels or sessions). This rigorous acquisition and preprocessing protocol is designed to ensure that observed changes in theta/beta ratio, frontal midline theta, posterior alpha power, and ERP components can be interpreted as meaningful indices of cognitive engagement and restoration rather than artifacts of the recording setup.

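### Identical EEG processing does not equalise artefact that arises in only one arm, so residue can bias the real-versus-VR EEG contrasts

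*Protocol article*

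**What the plan says.** In EEG Recording and Preprocessing the protocol article argues in three steps.

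- Premise: "Because the same EEG hardware, montage, and preprocessing pipeline are used in both exposure conditions".
- Consequence: "any residual artifacts linked to the outdoor environment (eg, occasional muscle adjustments due to temperature) or to the VR headset will be treated symmetrically" and dealt with in the analysis. The example given is "sensitivity analyses excluding highly contaminated channels or sessions".
- Conclusion: acquisition and preprocessing are designed so that changes in the spectral and event-related measures "can be interpreted as meaningful indices of cognitive engagement and restoration rather than artifacts of the recording setup".

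Other parts of the article bear on this:

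- Study Design: "Participants will be randomly assigned to 1 of 2 exposure conditions: a real natural environment or an immersive VR-simulated natural environment".
- EEG Recording and Preprocessing: headset padding can press on frontal sites, and "if AF3/AF4 are partially obstructed, frontal alpha asymmetry will be computed from the canonical F3/F4 pair". Outcomes lists frontal alpha asymmetry among the primary EEG measures.
- EEG Recording and Preprocessing: "Resting-state baselines will be collected preexposure and postexposure (T0 and T1) with 2-minute eyes-open (fixation cross) and 2-minute eyes-closed recordings". It does not say where these recordings are made or whether the headset is worn.
- Physical Nature Exposure Condition: the cognitive and emotional assessments after exposure take place outdoors.
- Introduction: real nature is expected to show the stronger restoration signature.
- Statistical Methods: group × condition × time is the named primary contrast for alpha. Condition × time is named for the cognitive and ASRS outcomes. A time-resolved alpha analysis across the 20-minute exposure is exploratory.
- Discussion: muscle and motion artefact will persist in both settings. It is not described as differing between them.

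**The concern.** Processing two signals alike gives them the same residual contamination only if they were contaminated alike. The two sources the article names are different in kind, and each belongs to one condition. Whatever survives cleaning is therefore confounded with condition. The electrode rule adds a second arm-specific difference: substitution is triggered by the headset, so the pair behind a primary EEG measure can differ by arm although the montage is described as the same.

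At stake is the trial's central comparison. A real-versus-VR difference in alpha or theta could be muscle power outdoors or noise under the headset. The article's reasoning would still allow it to be reported as a difference in restoration.

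**Working it through.** **1. Where each source can occur.** Each participant receives one environment, so:

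| Source | Real-nature arm | VR arm |
|---|---|---|
| Outdoor artefact during exposure | possible | no |
| Headset artefact during exposure | no | possible |
| Headset-triggered switch from AF3/AF4 to F3/F4 | no | possible |
| Outdoor residue at T1 | possible (assessments outdoors; place of resting EEG not stated) | no |
| Headset residue at T1 | no | not established (headset wear not stated) |

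**2. Which contrasts are affected.** Write the observed change in log power for arm *a* (R real, V virtual) and diagnostic group *g* as a true change δ(a,g) plus residue r(a,g).

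- Condition × time estimates the true difference plus r(R) − r(V), averaged over groups. Any difference in residue between arms enters in full.
- Group × condition × time estimates the true three-way effect plus [r(R,ADHD) − r(V,ADHD)] − [r(R,control) − r(V,control)]. This is zero when the arm difference in residue is the same in both diagnostic groups.

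**3. Possible size.** The article gives no artefact figure to reproduce, so the shifts *b* below are assumptions, in SD of the T0–T1 change, in one arm, with no true effect. The Power section gives 80 participants (20 per cell), a two-sided α of .05, and 64 as the lower end of the required range.

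- SE for condition × time = √(2/(N/2)); at N = 80, √(2/40) = 0.224.
- SE for the three-way term = √(4/(N/4)); at N = 80, √(4/20) = 0.447.
- Rejection probability = Φ(b/SE − 1.96) + Φ(−b/SE − 1.96).
- Example, b = 0.2, condition × time, N = 80: b/SE = 0.894, so Φ(−1.066) + Φ(−2.854) = 0.143 + 0.002 = 0.145.

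| b (SD of change) | Condition × time, N = 80 | Condition × time, N = 64 | Three-way, shift in ADHD group only, N = 80 |
|---|---|---|---|
| 0.1 | 7.3% | 6.9% | 5.6% |
| 0.2 | 14.5% | 12.6% | 7.3% |
| 0.3 | 26.9% | 22.4% | 10.3% |
| 0.49 | 59.2% | 50.0% | 19.5% |

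If the shift is equal in both diagnostic groups, the three-way rate stays at 5%.

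**4. What such shifts mean in power.** The planning effect reproduces: (7.88 − 6.93)/√((2.04² + 1.83²)/2) = 0.95/1.938 = 0.49. With the stated correlation of 0.5, the SD of change is √(2.04² + 1.83² − 2·0.5·2.04·1.83) = 1.944, so the effect is 0.95/1.944 = 0.489 SD of change. In log power it is about 2·ln(7.88/6.93) = 0.257, taking the ratio of means. Residue adding an assumed 5%, 10% or 20% to 8–13 Hz power in one arm shifts log power by ln 1.05 = 0.049, ln 1.10 = 0.095 or ln 1.20 = 0.182. That is 19%, 37% or 71% of 0.257. Multiplied by 0.489, it is roughly 0.09, 0.18 or 0.35 SD of change, about the range of the first three rows above.

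**5. Exclusion on contamination.** Assume contamination X and outcome change Y are standard normal with correlation ρ, and that the most contaminated 25% of one arm and 5% of the other are excluded. The mean of X among those kept is −φ(z)/q: −0.3178/0.75 = −0.424 and −0.1031/0.95 = −0.109. The bias is ρ × (−0.424 + 0.109) = −0.315ρ. This is 0 at ρ = 0, about 0.09 SD at ρ = −0.3 and about 0.16 SD at ρ = −0.5. A simulation of 2,000,000 draws gave −0.001, 0.095 and 0.157.

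**The case against.** The article says residual artefact is handled symmetrically, not that it becomes symmetric, and its sentence on interpretability states a design aim. It lists many safeguards: seated exposure with restricted motion, strap adjustment, impedance checks, topographical inspection, independent component analysis, epoch rejection, digitised positions for substituted electrodes, and a midline chain kept in everyone. Outdoor conditions are logged for sensitivity and exploratory analysis. The Discussion admits that artefact will persist. Further artefact modelling could sit in an analysis plan that is not shown.

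Most of this stands, and it limits the point. The safeguards should reduce residue. None of them makes it equal between arms, and the article still derives interpretability from sameness of equipment and pipeline. That is a stated inference and not an omitted detail.

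A reader might also infer that the plan drops sessions by arm and so breaks the randomised comparison. The text does not support this. The criterion is level of contamination, it is offered as an example of a sensitivity analysis, and the main analysis is intention-to-treat. Exclusion may differ by arm because the causes do, and it then biases the comparison only if contamination is related to outcome.

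**Conclusion.** The symmetry inference fails. Residue from arm-specific sources can bias condition and condition × time contrasts for EEG, and comparisons of alpha during exposure. The headset-triggered substitution adds an arm-specific difference to frontal alpha asymmetry.

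The size is unknown. The false-positive rates of about 7% to 27% for shifts of 0.1 to 0.3 SD at N = 80 rest on assumed shifts and a normal approximation. The 19% to 71% figures set a one-arm shift against a within-person pre-post effect. They are not the bias in the primary contrast.

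Two stronger readings go too far. One is that the primary alpha result is itself compromised: in group × condition × time the residue cancels if it is equal in both diagnostic groups, and the article neither shows nor rules out that it is. The other is that headset noise contaminates the pre-post change: this is established only for EEG recorded during exposure. Outdoor residue may reach T1, but the place of the resting recording is not stated.

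This is a worthwhile, inexpensive correction to what the EEG comparison may be said to show.

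**What to change.** 1. Delete the inference from identical processing to symmetric artefact. State instead that outdoor and headset sources are specific to one arm and may leave unequal residue.
2. Run the planned condition × group × time model on artefact indices already in the data: log 30–45 Hz power at the same sites, counts of rejected epochs and removed components, and substituted or excluded channels. Report them by arm.
3. Fix the consequence in advance. If an index differs by condition (or by condition × group, for the three-way contrast), state that the corresponding alpha or theta contrast cannot be separated from artefact. State also that a null check does not prove absence of artefact.
4. Keep contamination-based exclusion as a sensitivity analysis only. Report exclusions by arm and label them as potentially arm-dependent.
5. Label any model that adjusts for change in 30–45 Hz power as exploratory, because condition also affects that variable.
6. Compute frontal alpha asymmetry from F3/F4 in both arms, at least as a sensitivity analysis.

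The cost is a few extra model runs, with no new data. The 30–45 Hz band carries some neural signal and may miss noise from headset pressure, so it is an imperfect index in both directions.

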#### Data Management and Confidentiality

All study data will be pseudonymized using unique participant IDs before analysis. Identifiable information (eg, consent forms and contact details for follow-up reminders) will be stored separately from research data on encrypted, password-protected institutional servers with access restricted to the core research team. Neureka app data will be stored on secure servers hosted by Trinity College Dublin and exported only in deidentified form. In line with GDPR and institutional policies, deidentified research data will be retained for 10 years and then securely destroyed. Study findings will be communicated in aggregate form to participating clinical teams and, on request, to individual participants via a plain-language summary. Results will also be disseminated through peer-reviewed publications, conference presentations, and an update to the trial registry record once outcomes are available.

Given the minimal-risk, single-session behavioral nature of this study, no independent data monitoring committee will be established; study conduct and protocol adherence will instead be overseen by the principal investigator and study team in line with institutional and ethics-committee requirements. No formal interim analyses or statistical stopping rules are planned, but the principal investigator and the research ethics committee retain the authority to pause or terminate the study early should any unanticipated safety concerns arise.

### Statistical Analysis

#### Outcomes

The primary outcomes of this study will be: (1) changes in indices of neural restoration and engagement (parietal-occipital alpha power, frontal midline theta, and frontal alpha asymmetry) from preexposure to postexposure; (2) performance on two cognitive tasks: Meta Mind (confidence score, accuracy, and reaction time) to evaluate metacognition, and Star Racer (completion time, error rate, and task-switching cost) to measure cognitive flexibility and executive control; and (3) ADHD symptom severity, assessed by ASRS, included in both diagnostic group comparisons and dimensional modeling across the full sample.

Secondary outcomes will include exploratory trajectories of emotional well-being assessed through EMA, as well as self-reported nature connectedness (NCI) and weekly real-life contact with natural environments. These repeated measures are intended to characterize short-term decay or change patterns after a single exposure. Clinical change in the group with ADHD will be measured with the ACOS-Self, and quality of life with the AAQoL. Measures of VR tolerability and cybersickness (VRSQ) will be analyzed descriptively and, where appropriate, as covariates to aid interpretation of cognitive and EEG outcomes.

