**Methods:**

A total of 80 adults (40 with a confirmed ADHD diagnosis and 40 neurotypical controls) will be recruited and randomly assigned to either a real nature condition or an immersive VR-simulated nature condition. After a baseline assessment, participants will complete a 20-minute seated exposure in the assigned condition while 32-channel mobile electroencephalography (EEG) is recorded. Immediately post exposure, they will complete gamified cognitive tasks assessing cognitive flexibility and metacognition, self-report measures of mood, perceived restoration, simulator sickness, and nature connectedness. ADHD symptomatology and functional impact will be assessed with standardized scales at preexposure and postexposure and at the final follow-up. Ecological momentary assessment of emotional well-being, weekly self-reports of real-world nature and VR exposure, and repeated nature connectedness ratings will be collected via a mobile app over an 8-week follow-up period to characterize the decay or maintenance of effects. EEG analyses will focus on alpha-band markers of cognitive restoration, complemented by dimensional modeling of ADHD symptoms in linear mixed-effects models. The study has been preregistered on the Open Science Framework and will be prospectively registered with the Australian New Zealand Clinical Trials Registry (ANZCTR) before enrollment of the first participant. Ethical approval has been received from the Research Ethics Committee at Sligo University Hospital.

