Based on the literature and the theoretical framework outlined above, we hypothesize that both real and VR-simulated nature will acutely improve attention, cognitive flexibility, and mood and will be accompanied by EEG changes consistent with restoration, but that real nature will show stronger signatures of low-effort, bottom-up restoration than VR. We further expect that adults with ADHD will show equal or greater cognitive and affective gains than neurotypical adults after both real and VR-simulated nature, while displaying distinct patterns of prefrontal and parietal EEG change, reflecting different regulatory mechanisms. More tentatively, we anticipate that individual differences in ADHD-related symptoms will shape both the size and the time course of these effects: higher symptom levels may be linked to larger immediate benefits from nature exposure, but also to a faster decline of gains over the follow-up period, and the pattern of attenuation may differ between real and virtual nature along the continuum from neurotypical adults to those with more pronounced ADHD traits. Together, these aims position the study to clarify where responses to real and virtual nature converge, where they diverge, and under which conditions VR-based nature exposure is a suitable supplement to real-world nature for adults with higher ADHD traits.

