#### Cognitive Assessments

Meta Mind: a gamified metacognitive task in which participants make confidence judgments after completing a series of perceptual decisions involving dot quantity discrimination [73].

Star Racer: a gamified adaptation of the Trail Making Test [74], designed to measure cognitive flexibility and executive control through alternating visuospatial tracking and task-switching components.

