#### Statistical Methods

All analyses will follow an intention-to-treat approach and will be conducted using R (R Foundation for Statistical Computing). Statistical tests will be 2-tailed with a significance level of α=.05. Descriptive statistics will summarize sample characteristics. Baseline group differences will be assessed using Pearson chi-square tests for categorical variables and independent-samples *t* tests (or nonparametric equivalents) for continuous variables. Any variables showing systematic baseline imbalance will be considered as covariates in sensitivity analyses.

To evaluate the primary outcomes—changes from preexposure (T0) to immediate postexposure (T1) in EEG alpha power, cognitive performance (Meta Mind and Star Racer), and ASRS, we will implement linear mixed-effects models (LMMs) using the *lme4* package. Fixed effects will include exposure condition (real vs VR nature), diagnostic group (ADHD vs neurotypical), time (T0 vs T1, with T9 added where relevant to examine short-term maintenance), and their interactions. Participant will be entered as a random intercept; random slopes for time will be added where supported by convergence and model fit. The primary contrasts of interest are: (1) group × condition × time for alpha power in predefined frontal and parietal regions of interest, and (2) condition × time and group × time interactions for cognitive and ASRS outcomes.

For EEG data, log-transformed alpha power (8-13 Hz) will be averaged within each region of interest and exposure phase. Within-subject change scores (T1-T0, and T9-T0 where applicable) will be analyzed in the LMM framework described above. Exploratory time-resolved effects across the 20-minute exposure will be examined using cluster-based permutation tests on epoch-wise alpha power, with family-wise error controlled at 0.05. Effect sizes will be reported as Cohen *d* for pairwise contrasts and partial eta squared (η^2^_p_) for omnibus tests.

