Secondary outcomes include trajectories of emotional well-being assessed via weekly EMA, clinical functioning in the group with ADHD (ACOS-Self), quality of life (AAQoL), and nature connectedness (NCI). EMA scores over T0-T9 will be modeled with LMMs including fixed effects for time (treated as a continuous or categorical variable depending on fit), condition, group, and their interactions, with random intercepts for participants. ACOS-Self, AAQoL, and NCI change from T0 to T9 will be analyzed using separate LMMs with fixed effects for group, condition, and their interaction. Self-reported real-world nature and VR exposure during follow-up will be explored as time-varying covariates in additional models to probe their contribution to decay or maintenance of effects.

To incorporate a dimensional perspective, *z*-scored ASRS total and subscale scores will be included as continuous predictors in a restricted set of prespecified models [85] (eg, ASRS × condition × time interactions for alpha power and cognitive outcomes). These analyses will test whether attentional trait variation predicts sensitivity to environmental exposure across the full sample, without overparameterizing models.

Multiple-comparison control will be applied at the level of outcome families: EEG (regions of interest and key contrasts), cognitive tasks (Meta Mind and Star Racer indices), EMA trajectories, and clinical measures. Within each family, *P* values will be adjusted using false discovery rate procedures; unadjusted and adjusted values will both be reported.

Model assumptions (normality of residuals, homoscedasticity, and, where relevant, sphericity) will be checked using diagnostic plots and formal tests. If assumptions are violated, transformations or robust alternatives will be considered. Missing data will primarily be handled within the mixed-model framework under a missing-at-random assumption. In addition, sensitivity analyses will be conducted using multiple imputation and complete-case subsets (participants with data at least up to T1 and T9) to examine the impact of attrition on key inferences.

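### If the confidence score is the plain rating, the primary Meta Mind indices, analysed separately, do not capture metacognitive sensitivity or calibration, and confidence has no stated favourable direction

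*Protocol article*

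**What the plan says.** In the protocol article, the Outcomes section under Statistical Analysis makes "performance on two cognitive tasks: Meta Mind" and Star Racer a primary outcome. For the first task it names the indices and their purpose: "Meta Mind (confidence score, accuracy, and reaction time) to evaluate metacognition". The Cognitive Assessments section describes a task in which "participants make confidence judgments after completing a series of perceptual decisions involving dot quantity discrimination". The Methods paragraph of the abstract likewise speaks of "gamified cognitive tasks assessing cognitive flexibility and metacognition".

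The Statistical Methods section puts the cognitive outcomes into linear mixed models. The primary contrasts are "condition × time and group × time interactions for cognitive and ASRS outcomes", and "Statistical tests will be 2-tailed with a significance level of α=.05". For multiplicity, "cognitive tasks (Meta Mind and Star Racer indices" form one false-discovery-rate family.

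The article does not define the confidence score, name any index that relates confidence to correctness, say which direction of change in confidence is favourable, or say whether difficulty is adapted to hold accuracy constant.

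**The concern.** In a task that asks for a decision and then a confidence rating, metacognition has at least three parts. Sensitivity is how well confidence separates correct from wrong trials. Calibration is how close confidence lies to actual accuracy. Bias is the general level of confidence. Accuracy and reaction time belong to the first-order decision. Confidence level, taken alone, is the bias part. Sensitivity and calibration both need confidence and correctness to be combined, and the list contains no combined index.

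Direction is a separate problem. The indices are introduced as performance, yet a rise in confidence brings an underconfident person closer to calibration and takes an overconfident person further away. If the two diagnostic groups started on opposite sides, a group × time effect on confidence could not be read as gain or loss for either.

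The risk is that a shift in how freely people use the rating scale is reported as changed metacognition, while a change in insight that leaves accuracy and confidence level alone does not appear in the primary results.

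**Working it through.** The article gives no figure to reproduce on this point. The question is whether the listed indices, each analysed on its own, determine metacognitive sensitivity.

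**Inputs.** From the article: the three indices, the construct they are listed for, and the two contrasts. Assumed, because the article gives no task settings: an equal-variance signal-detection model, d' = 1.1, a 6-point confidence scale with all categories used equally, and 400,000 simulated trials. Reaction time was not modelled.

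**Step 1: fix accuracy and confidence level.** Expected accuracy is Φ(d'/2) = Φ(0.55) = 0.709. Equal use of categories 1 to 6 gives mean confidence (1+2+3+4+5+6)/6 = 3.50.

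**Step 2: vary only how well confidence follows the evidence.** Confidence is the ranked value of |evidence| + noise. Sensitivity is the type-2 AUROC, the probability that a correct trial carries higher confidence than a wrong one, with ties counted as half.

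| Noise SD in confidence | Accuracy | Mean confidence | Mean confidence, correct / wrong | Type-2 AUROC |
|---|---|---|---|---|
| 0 | 0.709 | 3.50 | 3.80 / 2.77 | 0.672 |
| 0.5 | 0.709 | 3.50 | 3.73 / 2.93 | 0.634 |
| 1 | 0.709 | 3.50 | 3.66 / 3.11 | 0.591 |
| 2 | 0.709 | 3.50 | 3.59 / 3.28 | 0.551 |
| 5 | 0.709 | 3.50 | 3.54 / 3.41 | 0.522 |
| noise only | 0.709 | 3.50 | 3.50 / 3.51 | 0.498 |

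The two listed indices are the same in every row, while sensitivity runs from its ceiling under this model to none. A second simulation with other assumed settings (accuracy 0.80, mean confidence 75 on a 50 to 100 scale) gave a range of 0.50 to 0.76, with the correct-minus-wrong confidence gap running from about 0 to 13.0 points.

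**Step 3: shift confidence only.** Noise is held at 0.5, ratings are treated as continuous, and a constant is added to every rating with no ceiling applied.

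| Constant added | Mean confidence | Accuracy | Type-2 AUROC |
|---|---|---|---|
| 0 | 3.5 | 0.709 | 0.638 |
| 0.5 | 4.0 | 0.709 | 0.638 |
| 1.0 | 4.5 | 0.709 | 0.638 |

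Confidence moves by up to a full point while insight does not move at all.

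**Step 4: direction.** Put confidence c and accuracy a on one scale, so that miscalibration is |c − a|. A small rise in c reduces |c − a| when c < a and increases it when c > a. The sign of a change in c therefore says nothing about benefit unless c is compared with a, and the listed contrasts do not make that comparison.

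**The case against.** **The word mean is not in the text.** The confidence score could be a derived score set out in the cited task source or in the preregistration, neither of which is shown. This stands, and the point is conditional on it. Even so, a score listed beside accuracy and reaction time reads most naturally as the plain rating. The same sentence also names a derived index for Star Racer, the task-switching cost, so derived measures are specified at this level of the article.

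**Confidence level is itself a facet of metacognition.** This stands too. A reader might infer that the three indices measure no metacognition at all, or that the trial cannot show anything about it. The documents do not support that. Bias is part of the construct. If confidence and accuracy share a scale, average over- or underconfidence follows from the two. The decisions and ratings needed for a linking index appear to be collected.

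**Adapted difficulty.** If difficulty is adapted, a change in confidence is easier to interpret. That is true, but it would still be a change in bias, not in sensitivity.

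**No directional claim is made for metacognition.** The improvement hypothesis in the Introduction says "both real and VR-simulated nature will acutely improve attention, cognitive flexibility, and mood" and names neither metacognition nor confidence, and the tests are 2-tailed. So the plan does not contradict a stated hypothesis. A 2-tailed test, however, only detects a shift; it does not say whether the shift is good.

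**The simulations are not trial quantities.** They show that separate averages do not fix a joint relationship. Their ranges depend on assumed settings, and they do not estimate how often this study would be misled.

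**Conclusion.** The point holds in a limited form. Provided the confidence score is the plain rating and each index is analysed separately, the primary Meta Mind outcome does not capture metacognitive sensitivity or calibration, and a condition × time or group × time effect on confidence cannot by itself be called better or worse metacognition. The defect lies in the listed endpoint, not in the data.

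Its size for this trial cannot be given, because the article states neither the trial count, nor the rating scale, nor whether difficulty is adapted. The range of 0.50 to 0.67 (or 0.50 to 0.76) for type-2 AUROC at identical accuracy and confidence illustrates what the listed indices leave open and is not a forecast. The matter should be settled before data are collected, but it reaches only the interpretation of Meta Mind. The alpha-power, Star Racer and ASRS outcomes and the sample-size calculation do not depend on it.

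**What to change.** Prespecify one index that links confidence to correctness as the Meta Mind metacognition outcome, computed from the decisions and ratings the task already elicits, and state its direction of benefit:

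- If the number of trials supports a per-person estimate: type-2 AUROC or meta-d'/d', higher being better. If accuracy differs between T0 and T1, use meta-d'/d' or adjust for accuracy.
- If trials are too few: either a calibration index (confidence minus accuracy on a common scale, closer to zero being better), or a trial-level mixed model of accuracy on confidence in which the slope may differ by condition, group and time, a steeper slope being better.

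Define the confidence score. Keep confidence level as a supporting descriptor labelled as bias with no direction of benefit, alongside accuracy and reaction time. If no linking index is feasible, relabel the outcome as confidence and perceptual performance and draw no conclusion about metacognitive gain.

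The cost is a wording change and one derivation, with the registrations updated before data collection. The false-discovery-rate family need not grow: it now holds 3 + 3 = 6 task indices, and would hold 1 + 3 = 4 if the other Meta Mind indices become descriptors. The real downside is that a per-person index is noisier than an average when trials are few, so the trial count should be checked before the index is chosen.
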